### **6.2.2 Drug Infusions**

The drug administration system comprises 4 programmable syringe pumps, four 5-mL Plastipak syringes (Becton Dickinson), 4 sealed extension lines with male Luer attachments (each containing a septum) at one end, 4 double-sided syringe connectors with female Luer attachments (each holding an internal needle), 4 lengths of sealed drug administration tubing with male Luer attachments (each containing a septum) at both ends and a 4-channelled drug administration set. The latter comprises 4 needles mounted in a hub, each connected to independent bacteria and bubble filters and thence to short lengths of tubing, each with a female Luer attachment holding an internal needle. In addition, 3 syringe connectors with female Luer attachments at both ends and holding an internal needle at one end are used by the pharmacist preparing the study drug to fill the sealed extension lines and sealed drug administration lines.

Prior to drug administration, the pharmacist will fill the 4 lengths of drug administration tubing with an appropriate dose of drug (using 2 syringe connectors, one at each end of the sealed tubing), and label each line appropriately without identifying the treatment allocation. The pharmacist will further fill 4 syringes with aCSF, connect them to the open ends of the extension lines and fill the extension lines (using a single syringe connector at the opposite end to evacuate air). All syringe connectors will be disconnected and discarded once all lines have been filled. The filling of devices will take place up to 48 hours before a planned drug infusion.

For the infusion, each syringe/sealed extension line assembly will be connected to a double-sided-syringe connector, then to a drug administration line, then to one of the 4 channels of the drug administration set which prior to this has been flushed with aCSF.

Connection of the drug administration set to the port begins with the health professional cleaning the port and the immediate surrounds with an aseptic technique. The cylindrical needle hub of the drug administration set will be positioned over the port and locked to the port using a socket screw key. The 4 needles will be lowered through the port septum by use of a hand-tightened nut and thence individually guided into their separate channels that conduct the drug to identifiable catheters.

Once the connection has been secured, study medication is administered as detailed in Section 6.3. When the infusion is complete after approximately 90 to 150 minutes the administration set will be disconnected from the port by unscrewing both the nut and the socket screw.

### **6.3 Double-Blind Treatment**

Subjects will receive either GDNF or placebo infusions every 4 weeks for 9 months:

- Group A, active treatment: 600  $\mu$ L of 0.20  $\mu$ g/ $\mu$ L GDNF in aCSF per putamen every 4 weeks
- Group B, placebo: 600  $\mu$ L of aCSF per putamen every 4 weeks.

Study treatments will be prepared by an unblinded pharmacist at the study site based on the randomisation. Ready to use preparations of GDNF or aCSF will be provided to the PI or designee in identical containers identifiable only by codes unknown to the PI or any other study staff. Drug preparations guidelines are provided in a separate pharmacy manual.

At each treatment, infusion tubes will be connected with the transdermal port using standard aseptic technique. Every subject will receive study drug intrapatamenally titrated up to an infusion rate of 3-5  $\mu$ L/minute. The infusion rates will be up-titrated following a linear ramping scheme from 0  $\mu$ L/min to 3-5  $\mu$ L/min (0.18-0.30 mL/hour) over 30 to 40 minutes. The infusions will be delivered by the external syringe pumps with pre-programmed infusion algorithms (Perfusor® Space, B Braun, Melsungen, Germany).

Two catheters per putamen will be used, and 300  $\mu$ L of study drug will be delivered per catheter at each treatment. This amounts to a dose of 120  $\mu$ g GDNF per putamen per

administration in active subjects. An aCSF “flush” of up to 100  $\mu$ L per catheter (at 3-5  $\mu$ L/min) will clear the dead space of the implanted system after each infusion.

The infusions will be delivered by trained personnel. During the infusion, subjects will be semi-recumbent in a reclining chair. The total procedure time for the completion of the infusions will be approximately 90 to 150 minutes depending on potential reflux parameters observed on post infusion MRIs.

#### **6.4 Compliance with Study Treatment**

All treatments will be administered by PI or designee. Administration records will be kept on site, and administration information, including time and date of infusion, identification (blinded) of the infusate, infusion rate and duration, and the reasons for any interruptions of the infusion or for any missed or omitted infusions will be recorded in the CRF.

#### **6.5 Accountability of the Study Treatment**

It is forbidden to use investigational drug material for purposes other than as defined in this protocol.

All supplies of study medication will be accounted for in accordance with GCP. There will be an individual study drug accountability record for each subject and the pharmacist is to maintain accurate records of the disposition of all study medication supplies received and dispensed during the study. These records will include the amounts and dates clinical drug supplies were received, dispensed to the PI or designee for any given subject, and returned to the manufacturer. If errors or damages in the clinical drug supply shipments occur, the pharmacist will notify the manufacturer immediately so that corrective action can be taken as needed. Copies of the study medication accountability records will be provided by the pharmacist for inclusion in the Trial Master File (TMF) after database lock. The study monitor will periodically check the supplies of study medication held by the pharmacist to verify accountability of all medication used.

The PI or designee will administer the medication only to the identified subjects of this study, according to the procedures described in this study protocol. After the end of the study, all unused medication and all medication containers can be destroyed on-site as

long as proper documentation is supplied. If destruction on-site is not possible then medication and all medication containers will be returned to the manufacturer for destruction and documentation will be returned to the manufacturer. The manufacturer will verify that a final report of drug accountability is prepared and maintained in the Investigator's Study Centre File.

## **6.6 Test Infusions**

A test infusion of diluent will be administered at the end of the healing period in all subjects. In Primary Study Stage subjects, the test infusion will contain gadolinium contrast. A repeat test infusion of gadolinium contrast-containing diluent will be given to Primary Study Stage subjects at Week 40.

The infusions will be freshly prepared on site prior to use following the steps described for study medication above. Specifically, for Primary Study Stage subjects, 4 lengths of drug administration tubing (each holding 300  $\mu$ L) will be filled 2 mM gadopentetate dimeglumine (1:250 dilution of Magnevist®). The drug administration lines will then be connected as specified in Section 6.2.2, and the infusate will be delivered according to the infusion protocol provided in Section 6.3.

## **6.7 Concomitant Medication**

Subjects should have PD medication optimized and stabilized prior to study entry. Every effort should be made not to increase subjects' medication for PD during the study, but medication may be increased if required for to maintain the subject's well being. PD medication dose may be decreased at the discretion of the PI to manage PD drug-related side-effects. Non-PD medications may be altered at any time at the PI's discretion.

Throughout the study the PI may prescribe any concomitant medications or treatments deemed necessary to provide adequate supportive care.

Any medication other than the study medication, including prescription or over-the-counter medications, vitamins and herbal medications taken during the study will be recorded in the CRF with their indications.

## **7 SAFETY REPORTING**

### **7.1 Definitions**

#### **7.2 Adverse Event (AE)**

An AE or adverse experience is:

Any untoward medical occurrence in a subject or clinical investigation participant administered a medicinal product, which does not necessarily have a causal relationship with this treatment (the study medication).

An AE can therefore be any unfavourable and unintended sign (including an abnormal laboratory finding), symptom or disease temporally associated with the use of the study medication, whether or not considered related to the study medication.

#### **7.3 Adverse Reaction (AR)**

All untoward and unintended responses to a medicinal product related to any dose.

The phrase "responses to a medicinal products" means that a causal relationship between a study medication and an AE is at least a reasonable possibility, i.e., the relationship cannot be ruled out.

All cases judged by either the reporting medically qualified professional or the Sponsor as having a reasonable suspected causal relationship to the study medication qualify as ARs.

#### **7.4 Serious Adverse Event (SAE)**

An SAE is any untoward medical occurrence that at any dose:

- Results in death
- Is life-threatening; NOTE: The term "life-threatening" in the definition of "serious" refers to an event in which the participant was at risk of death at the time of the event; it does not refer to an event which hypothetically might have caused death if it were more severe.
- Requires inpatient hospitalisation or prolongation of existing hospitalisation
- Results in persistent or significant disability/incapacity

- Is a congenital anomaly/birth defect
- Other important medical events; NOTE: Other events that may not result in death, are not life-threatening, or do not require hospitalisation, may be considered an SAE when, based upon appropriate medical judgement, the event may jeopardise the subject and may require medical or surgical intervention to prevent one of the outcomes listed above.

To ensure no confusion or misunderstanding of the difference between the terms "serious" and "severe," which are not synonymous, the following note of clarification is provided:

The term "severe" is often used to describe the intensity (severity) of a specific event (as in mild, moderate, or severe myocardial infarction); the event itself, however, may be of relatively minor medical significance (such as severe headache). This is not the same as "serious," which is based on subject/event outcome or action criteria usually associated with events that pose a threat to a participant's life or functioning as defined in the bullet points above. Seriousness (not severity) serves as a guide for defining regulatory reporting obligations.

### **7.5 Serious Adverse Reaction (SAR)**

An AE (expected or unexpected) that is both serious and, in the opinion of the reporting Investigator, believed with reasonable probability to be due to one of the study treatments, based on the information provided.

### **7.6 Suspected Unexpected Serious Adverse Reaction (SUSAR)**

An SAR, the nature or severity of which is not consistent with the applicable product information (e.g., Investigator's Brochure for an unapproved investigational product or Summary of Medicinal Product Characteristics [SMPC] for an approved product).

### **7.7 Causality and Expectedness**

The relationship of each AE to the trial medication must be determined by a medically qualified individual according to the following definitions:

**Related:** The AE follows a reasonable temporal sequence from trial medication administration. It cannot reasonably be attributed to any other cause.

**Not Related:** The AE is probably produced by the participant's clinical state or by other modes of therapy administered to the participant.

The expectedness of each **SAE** in the trial must be determined by a medically qualified individual according to the following definition:

**Unexpected Adverse Drug Reaction:** An adverse reaction, the nature or severity of which is not consistent with the applicable product information (i.e., Investigator's Brochure).

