### **5.2.5 Safety Endpoints**

- Frequency of device-related adverse events (AEs) during the study period
- Frequency of treatment-emergent AEs (all treatment-emergent AEs and treatment-emergent AEs related to study drug) during the study period.
- Frequency of dyskinesias, falls, adverse changes in mood, and impulsivity reported as treatment-emergent AEs during the study period (AEs of special interest).
- Change from baseline in the Questionnaire for Impulsive-Compulsive Disorders in Parkinson's Disease (QUIP) every 8 weeks.
- Change from baseline in the Montreal Cognitive Assessment (MoCA) after 9 months of double-blind treatment.
- Change from baseline in the Mattis Dementia Rating Scale (MDRS) after 9 months of double-blind treatment.
- Adverse changes in MRI findings as captured by AE reporting.
- Frequency of subjects with anti-GDNF antibodies during the study.
- Results of routine laboratory blood tests (haematology, serum chemistry) and urinalysis performed at baseline and at intervals during the trial.

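### Sections 7.3, 7.5 and 7.7 set three incompatible causality thresholds, and the strictest, whose two categories leave a gap, is the one applied to every AE

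*Protocol*

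**What the plan says.** All the relevant text is in the protocol.

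- **Section 7.3 (adverse reaction).** The test is met where a "causal relationship between a study medication and an AE is at least a reasonable possibility, i.e., the relationship cannot be ruled out". The section adds that a case qualifies if it is "judged by either the reporting medically qualified professional or the Sponsor as having a reasonable suspected causal relationship", so one of the two judgements is enough.
- **Section 7.5 (serious adverse reaction).** The event must be serious and, in the reporting investigator's opinion, "believed with reasonable probability to be due to one of the study treatments". The sponsor's judgement is not mentioned here.
- **Section 7.6 (SUSAR).** It is defined as "An SAR, the nature or severity of which is not consistent with the applicable product information", so it inherits the causality test of 7.5.
- **Section 7.7 (causality).** This is the working rule: "The relationship of each AE to the trial medication must be determined by a medically qualified individual according to the following definitions". There are two categories. Related requires a plausible time relation to dosing plus a second condition: "It cannot reasonably be attributed to any other cause". Not Related is worded: "The AE is probably produced by the participant's clinical state or by other modes of therapy administered to the participant".

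The causality call is then used in three places. Section 5.2.5 lists the frequency of "treatment-emergent AEs related to study drug" among the safety endpoints. Section 7.8 requires AEs related to drug or device to be followed until they resolve or stabilise. Section 7.10 sets reporting of fatal or life-threatening SUSARs within 7 days and of other SUSARs within 15 days.

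**The concern.** The three wordings do not express one standard. Section 7.3 implicates the drug unless it can be excluded. Section 7.7 implicates the drug only if everything else can be excluded. Section 7.5 lies between them. Nothing elsewhere in the protocol says which prevails, and an assessor who follows 7.7 must decline to call Related some events that 7.3 calls reactions.

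This matters in a trial where other explanations are easy to find. Participants have fluctuating Parkinson's disease on dopaminergic medication, four implanted catheters, a skull-mounted port, and repeated infusions through that hardware. That alternative explanations will often be available is my inference, not a statement of the protocol. At stake are one safety endpoint, the follow-up of related events, and possibly the expedited reporting of a serious unexpected event for an experimental intracerebral drug.

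**Working it through.** No arithmetic applies: the protocol gives no figure for causality classification, and none is needed to establish the contradiction. The check is to take the possible kinds of event and read each section's test against them.

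| Event, with a plausible time relation to an infusion | 7.3 | 7.7 |
|---|---|---|
| A. No other reasonable cause | Reaction | Related |
| B. Another cause plausible but not probable | Reaction: the drug cannot be ruled out | Neither: fails Related because another cause is reasonable, fails Not Related because that cause is not probable |
| C. Another cause probable, drug not ruled out | Reaction, on the cannot-be-ruled-out reading | Not Related |
| D. Another cause probable, drug ruled out | Not a reaction | Not Related |

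The sections agree on A and D and disagree on B and C. In both disagreements 7.7 removes an event from the related group that 7.3 would include. In none of these four cases does it add one, so the direction is fixed even though the amount is not.

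Section 7.5 gives a third answer. Event B may satisfy it, if the drug is thought the more likely cause. Event C probably does not. So B can be a serious adverse reaction under 7.5 while having no valid code under 7.7.

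Tracing the use of the call:

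1. **Endpoint, Section 5.2.5.** The frequency of drug-related treatment-emergent AEs excludes B and C if 7.7 is followed, and includes them if 7.3 is followed.
2. **Follow-up, Section 7.8.** The duty to follow an event to resolution or stability attaches to related events, so it narrows in the same way.
3. **Expedited route, Sections 7.5, 7.6 and 7.10.** A SUSAR must first be a serious adverse reaction in the reporting investigator's opinion. If the investigator takes the 7.7 code as that opinion, a serious unexpected event of type B or C can miss the 7- or 15-day route.
4. **Device, Sections 5.2.5 and 7.8.** Section 7.8 already requires relatedness to medication or device to be assessed, but the definitions in 7.7 are worded for trial medication only. A device cause also counts as another cause under 7.7, which removes the event from drug-related.

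Three things do not use the call. AEs are recorded whatever their attribution (Section 7.8). Dyskinesias, falls, mood change and impulsivity are counted as treatment-emergent AEs with no relatedness condition (Section 5.2.5). All SAEs go to the trust's research office within 1 working day (Section 7.9).

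**The case against.** The best case on the other side is that little depends on the wording. The placebo comparison of AEs, including those of special interest, is made on all treatment-emergent events. Every SAE reaches the research office and is reviewed at the next Trial Safety Group meeting. Section 7.3 lets the sponsor judge an event a reaction on its own account, and an independent data monitoring committee watches safety (Section 8.4). Section 7.5 has its own test and does not cite 7.7. Section 7.3 itself closes on a suspected-relationship wording narrower than cannot be ruled out.

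Most of this stands, and it limits the point. A reader might go further in three ways that the protocol does not support.

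- One might infer that special-interest events would almost never be counted, because Parkinson's disease or levodopa can explain them. They are counted regardless of cause. Only their share of the related subset is exposed, and 7.7 does not say how an event of type B must be coded.
- One might infer that a serious event that is a reaction under 7.3 would not enter the SUSAR route. That 7.7 governs that step is plausible but not stated, and the safeguards above are real. It could be missed; more cannot be said.
- One might attach a size by assuming that, say, 50% to 90% of special-interest events have another explanation. That only returns the assumption as the result, and it says nothing about serious unexpected events, which are a different set.

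The safeguards do not remove the contradiction. The sponsor's judgement is written into 7.3 but not into 7.5, through which SUSAR status runs. Receipt of an SAE at the research office is not the same as expedited reporting. Blinding may spread the misclassification over both arms, but it does not restore the events to the related count.

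**Conclusion.** The contradiction is on the face of the protocol. Three sections set three incompatible thresholds, the mandatory one is the strictest, and its two categories are not exhaustive. Followed as written, 7.7 understates the drug-related AE endpoint and narrows the follow-up duty. It could also, if investigators carry the 7.7 code into the 7.5 judgement, keep a serious unexpected event off the 7- or 15-day route.

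The direction follows from the text. The size cannot be derived from it, and I give none. The efficacy endpoints, total and special-interest AE counts and SAE reporting to the research office are not affected. The conclusion assumes only that assessors apply 7.7 literally and that some events have both a possible drug cause and another reasonable cause.

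**What to change.** Reconcile Sections 7.3, 7.5 and 7.7 to one standard, the protocol's own in 7.3:

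- **Related:** a causal relationship is at least a reasonable possibility, so it cannot be ruled out.
- **Not Related:** there is no reasonable possibility of a causal relationship.

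These two categories cover every event. Use the same threshold in 7.5, and let either the investigator's or the sponsor's judgement suffice for a serious adverse reaction, as 7.3 already does for an adverse reaction. State that the same two definitions apply, separately, to the device assessment that 7.8 already requires.

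The cost is a wording amendment and short re-training of assessors. Related-AE counts will come out somewhat higher. Design, sample size and treatment do not change.

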## 7.8 Procedures for Recording Adverse Events

All AEs occurring during the study from the time of screening (first consent) until the Week 40 visit has been completed (or 28 days after the last dose of study medication for subjects who discontinue the study early), observed by the PI or designee or reported by the participant, whether or not attributed to study medication, will be recorded on the AE pages of the CRF.

The following information will be recorded: description, date and time of onset, date and time of end, occurrence during infusion, severity, assessment of relatedness to study medication or device, seriousness, action taken, and outcome. Follow-up information should be provided as necessary.

AEs considered related to the study medication or to the device as judged by the PI or a medically qualified designee will be followed until resolution or the event is considered stable. All related AEs that result in a participant's withdrawal from the study or are present at the end of the study, should be followed up until a satisfactory resolution occurs.

It will be left to the PI's or medically qualified designee's clinical judgment whether or not an AE is of sufficient severity to require the participant's removal from treatment. A participant may also voluntarily withdraw from treatment due to what he or she perceives as an intolerable AE. If either of these occurs, the participant must undergo an end of study assessment (unless he or she has withdrawn consent to do so) and be given appropriate care under medical supervision until symptoms cease or the condition becomes stable.

The severity of events will be assessed on the following scale:

1 = mild, 2 = moderate, 3 = severe.

The relationship of AEs to the study medication will be assessed by the PI or a medically qualified designee.

Any pregnancy occurring during the clinical study and the outcome of the pregnancy should be recorded and followed up for any congenital abnormality or birth defect.

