#### **5.1.1 Pilot Stage**

The purpose of the Pilot Stage is to ensure the safety of the surgical technique and study drug administration and, if necessary, optimise these prior to initiating the Primary Study Stage. Six subjects with PD of moderate severity will be randomised in a 2:1 allocation (total of 4 subjects receiving active GDNF and 2 subjects receiving placebo) to receive infusions of GDNF or placebo every 4 weeks in a double-blind fashion for 9 months (10 infusions; last infusion at Week 36). A safety review of these 6 subjects will be performed by both the independent Data Monitoring Committee (DMC) and the Medicines and Healthcare Products Regulatory Agency (MHRA) after the last pilot subject has completed 3 months of treatment. While the Pilot Stage is primarily aimed at confirming the safety of the study treatments and procedures and meeting regulatory requirements as articulated by the MHRA, it also serves to potentially optimise options for handling infusions in subjects allowing minor modifications of procedures in response to any surgical, technical, infusion, imaging or logistical issues that may be identified. Subjects randomised in the Pilot Stage will be analysed together with the subjects randomised in the Primary Study Stage as part of the safety and supplementary efficacy analyses but will not be included in the primary efficacy analysis.

**Figure 7 Study Schema**[figure not shown]

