## 5.5 Study Procedures

Planned study participation for each subject (both Pilot and Primary Study Stage cohorts) will comprise the following 4 periods:

- Presurgery: Up to 60 days
- Surgery and Healing: Approximately 8 weeks post-surgery (including 4 weeks recovery followed by a test infusion of diluent to confirm catheter function and drug distribution, and a further 4 week-interval before the first infusion of study drug), or longer if needed to meet the post-surgery randomisation criteria.
- Double-blind Treatment: GDNF or placebo infusions every 4 weeks for 9 months; the total dose of GDNF administered at any given infusion will be 240  $\mu$ g (600  $\mu$ L of 0.20  $\mu$ g/ $\mu$ L GDNF per putamen).

Volumetric catheter performance will be determined both by gadolinium contrast-enhanced T1-weighted and by T2-weighted and FLAIR 3T MRI scans throughout the study. The first post-infusion scan will be obtained following the test infusion of artificial CSF (aCSF) (diluent) approximately 4 weeks into the healing period and 4 weeks prior to the first planned infusion of study drug in all subjects. In Pilot Stage subjects, this will be T2-weighted and FLAIR MRI only. In Primary Study Stage subjects, the test infusion will contain 2 mM gadopentetate dimeglumine and be followed by a T1-weighted MRI scan in addition to the T2-weighted and FLAIR MRI scans. Pilot Stage subjects will further undergo post-infusion imaging with all study treatments. In Primary Study Stage subjects, no interim T2-weighted or FLAIR MRI monitoring will be done unless clinically mandated. At Week 40 (where no randomised drug administration is scheduled), Primary Study Stage subjects will receive another gadolinium contrast-containing test infusion of diluent, followed both by T1-weighted and by T2-weighted and FLAIR MRI scans. All post-infusion scans are to be completed within 2 hours following the infusion.

To allow for optimisation of infusion procedures in response to potential surgical, technical, infusion, imaging or logistical issues, Pilot Stage subjects will be receiving the test infusion of aCSF and the first infusion of study medication in the 3T MRI suite with real-time MR imaging. Rapid acquisition T2-weighted and FLAIR MRI scans will be performed at approximately 20 minute intervals during these infusions.

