## 8.7 Inclusion in Analysis

The primary analysis will be conducted after all Primary Study Stage subjects have reached the 9-month endpoint.

The primary analysis population will include all subjects randomised to the study in the Primary Study Stage of the study. The primary analysis will follow the ITT principle, with all subjects randomised in the Primary Study Stage included and grouped according to randomised treatment (regardless of treatment received). Subjects randomised in the Pilot Stage will not be included in the ITT population for the primary analysis as the treatment parameters may be altered during this phase.

In addition, efficacy analyses will be repeated on the ITT Overall Population comprising all randomised Primary Stage subjects and all randomised Pilot Stage subjects and on the Per Protocol Population, comprising all subjects treated in the study (i.e., including subjects randomised in the Pilot Stage) and without major protocol violations. Misrandomisations constitute major protocol violations.

The Safety Primary Population will comprise all Primary Study Stage subjects who received at least one dose of study medication, with subjects grouped according to treatment actually received. All safety analyses will be performed on the Safety Primary Population. More limited analyses will be performed for the Safety Overall Population comprising all subjects (both Pilot and Primary Study Stage) who received at least one dose of study medication, with subjects grouped by treatment actually received. Safety data for Pilot Stage subjects will be provided and evaluated via individual data listings. Pre-treatment AEs will be analysed in the Safety Enrolled Population comprising all enrolled subjects (Primary Study Stage and Pilot Stage subjects combined).

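### AE relatedness has no category for implantation surgery or contrast test infusions, and device-relatedness is undefined: the device-related count is ambiguous and Week 40 contrast AEs may be pooled or missed

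*Protocol*

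**What the plan says.** Section 7.8 lists what is collected for every AE. For cause, it is "assessment of relatedness to study medication or device". For timing, it includes "date and time of onset, date and time of end, occurrence during infusion". The same section says that AEs judged related to the drug or the device are followed until they resolve or are stable. It ends AE recording when the Week 40 visit is completed, or 28 days after the last dose for subjects who stop early.

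Section 7.7 defines causality for the drug only: "The relationship of each AE to the trial medication must be determined by a medically qualified individual according to the following definitions". The category for unrelated events reads: "The AE is probably produced by the participant's clinical state or by other modes of therapy administered to the participant".

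Section 5.2.5 makes two endpoints depend on these judgements. One is "Frequency of device-related adverse events (AEs) during the study period". The other is drug-related AEs, restricted to treatment-emergent ones. Section 8.7 analyses pre-treatment AEs separately, with both stages combined.

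On contrast, Section 5.5 states: "In Primary Study Stage subjects, the test infusion will contain 2 mM gadopentetate dimeglumine and be followed by a T1-weighted MRI scan". Pilot Stage test infusions are followed by T2-weighted and FLAIR scans only. Section 6.6 plans a second contrast test infusion in Primary Study Stage subjects at Week 40. Sections 5.6.4 and 5.6.5 allow it in a two-week window around Week 40, which Table 2, footnote b, gives as ±1 week.

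**The concern.** Subjects undergo three distinct exposures besides the study drug: a neurosurgical implantation, the implanted device, and test infusions into both putamina. Only the device has a relatedness item, and that item has no definition. One assessor could code a haemorrhage at implantation as device-related, and another could code it as unrelated to both drug and device. Both entries would comply with the protocol.

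This sits badly with the stated aim of the first stage: "The purpose of the Pilot Stage is to ensure the safety of the surgical technique and study drug administration". Surgical safety is an aim, but relatedness to surgery is not collected. Nor could the Pilot Stage safety review inform on intraputamenal contrast, because no Pilot Stage subject was planned to receive it.

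At stake are the meaning of one listed safety endpoint, the follow-up of some events, and the completeness of AE data after the last planned infusion. An analysis plan can re-sort recorded events by date. It cannot supply a causal judgement that was never made or an event that was never recorded.

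**Working it through.** The plan gives no figure to reproduce. The check sets the passages side by side.

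1. **Categories.** The table shows each exposure against Sections 7.7 and 7.8.

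| Exposure | Relatedness item (7.8) | Definition (7.7) |
|---|---|---|
| Study drug | yes | yes |
| Device | yes | none |
| Implantation surgery | none | none |
| Test infusion, diluent or contrast | none stated | none |

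The status of contrast is itself unclear. The synopsis names only GDNF in aCSF and aCSF alone as investigational products, yet Section 6.1, the study medication section, also describes the contrast agent. An assessor cannot tell whether a contrast event counts as related to study medication.

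2. **Exposure.** Primary Study Stage: 36 subjects × 2 test infusions = 72 planned contrast infusions, more if a test infusion is repeated after corrective action (Section 5.5.3). Pilot Stage: 0 of 6 subjects.

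3. **Drug-related endpoint.** By Section 5.5, surgery comes about 8 weeks, and the first test infusion about 4 weeks, before the first dose. New AEs from either are pre-treatment and stay out of the treatment-emergent count. For the drug question, Section 7.7 sends events with another cause to the unrelated category, which is the right answer. The only exposed period is Week 40.

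4. **Device-related endpoint.** It runs over the whole study period, so it includes surgery and healing. With no definition, surgical and infusion-procedure events may be counted in or left out. The count depends on a convention that is not stated.

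5. **Follow-up.** The follow-up sentence in Section 7.8 applies to AEs related to drug or device. An event judged due to surgery or contrast, and to neither of those, is outside it. Sections 5.10 and 7.8 also provide for events that lead to withdrawal, but not for such an event in a subject who continues.

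6. **Week 40.** The visit may be held within ±3 days of the scheduled date (Section 5.6.5), and the contrast infusion within ±7 days (Table 2, footnote b). At the extremes, the infusion follows the visit by 7 + 3 = 10 days. If the infusion comes before the visit is completed, its AEs occur after study dosing and, without a rule, would probably be counted as treatment-emergent. If it comes afterwards, AE recording has already ended.

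7. **What 36 subjects can show.** If all 36 receive contrast and none has an event, the one-sided 95% upper bound on the event rate is 1 − 0.05^(1/36) = 8.0%. For assumed true rates of 2%, 5% and 10%, the chance of at least one event, 1 − (1 − p)^36, is 52%, 84% and 98%. With so few subjects, unrecorded events matter.

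**The case against.** A reader might infer that the drug-related endpoint is misattributed, that contrast safety cannot be read out at all, or that every surgical or contrast event is assigned to the wrong cause. The documents support none of these.

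- Calling a surgical event unrelated to the drug is correct, and timing keeps surgery and the first test infusion out of the treatment-emergent period.
- Onset times and the infusion flag allow AEs after a test infusion to be found by date. Section 5.5.3 adds vital signs, the Glasgow Coma Scale, observation for at least 4 to 6 hours, and MRI within 2 hours.
- No passage gives a proportion of events wrongly assigned.

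Further points on the other side are fair. Implantation is described within the delivery-system section (6.2), so treating surgical events as device-related is a possible convention. Tables by stage are ordinarily left to the analysis plan. The AE page is not shown, and the protocol does not define treatment-emergent. The DMC may already recommend termination at any point for safety reasons (Section 8.4), so an extra DMC review would add little. Section 5.6.5 describes the second contrast infusion together with the Week 40 assessments, so one could argue that the visit is not complete until it has been given.

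What stands is narrower. The protocol itself fixes the list of causes, does not define device-relatedness, and does not say whether the Week 40 infusion falls inside the recording period. Each possible convention is reasonable, but none is stated.

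**Conclusion.** The point holds as an ambiguity in data collection with a recording gap at Week 40. The device-related AE count cannot be interpreted without a definition. Events judged due to surgery or contrast fall outside the stated follow-up. AEs after up to 36 second contrast infusions may be pooled with treatment-emergent AEs or go unrecorded.

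No between-arm bias is claimed: surgery and contrast are the same in both arms. Nor would a new category isolate a contrast effect. All 36 Primary Study Stage subjects are planned to receive contrast in the same diluent through the same device, and only 6 Pilot Stage subjects provide a contrast-free comparison. A relatedness item records a judgement; it does not create a control group.

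The conclusion assumes that the AE page follows Section 7.8, that all 36 subjects receive both contrast infusions, and that treatment-emergent is read in the usual way, as after the first dose. The matter is worth correcting but does not touch the primary efficacy analysis.

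**What to change.** - In Section 7.8 and on the AE page, add relatedness items for implantation surgery and for test infusion (diluent/contrast), and state what counts as device-related.
- State whether the follow-up sentence in Section 7.8 applies to events in the new categories.
- Apply the new items and the definition to AEs already recorded, before unblinding.
- Tabulate AEs after each test infusion in Primary Study Stage subjects, with those after the Week 40 test infusion shown separately from treatment-emergent AEs.
- Reconcile Sections 5.6.4 and 5.6.5 and Table 2, footnote b, with Section 7.8, so that AE recording covers the Week 40 test infusion whenever in its window it is given.

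The cost is two CRF items, a blinded re-attribution of recorded AEs, one extra safety table, and a short extension of AE recording in subjects whose test infusion follows the visit.
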